### Sample size

The sample size for this study was determined through statistical analysis using the G*Power 3.1 program. Based on the data analysis method, the test family was set to F-tests, and the statistical test was designated as ANOVA: repeated measures, within-between interaction. The effect size was determined according to Cohen’s method [26] and was set to 0.25, based on previous studies [27–29]. Initially, the significance level (α) was set at 0.05 for the sample size calculation. However, to account for multiple comparisons, the Bonferroni correction was applied, adjusting the per-comparison significance level to α = 0.0167. The statistical power (1-β) was set at 0.80, the number of groups at three, and the number of repeated measurements at three. Consequently, the required sample size was recalculated to be 45 participants (15 per group). To account for potential attrition, a 20% dropout rate was considered, based on rates observed in previous studies [30–32]. Therefore, the final total sample size was 54 participants, with 18 participants allocated to each group.

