### Statistical analysis

The normality of the primary variables will be assessed using the Shapiro-Wilk test, and homogeneity of variances will be evaluated using Levene’s test. If normality is satisfied, a repeated measures ANOVA will be performed to examine the main effects of time, group, and their interaction. Mauchly’s test for sphericity will be conducted, and if violated, the Greenhouse-Geisser correction will be applied. If the normality assumption is violated, non-parametric alternatives will be implemented. The Kruskal-Wallis test will be used for between-group comparisons at each time point, while the Friedman test will be applied for within-group repeated measures. To adjust for multiple comparisons, Bonferroni correction will be applied as needed to control for Type I error. If significant interaction effects are observed in the repeated measures analysis, post-hoc tests will be conducted. For parametric statistics, paired t-tests will be used to compare within-group differences over time, and independent t-tests will be performed to compare mean differences between groups at the same time points. For non-parametric statistics, the Mann-Whitney U test will be used to compare two groups at a specific time point, and the Wilcoxon signed-rank test will be employed to analyze within-group differences between two time points.

All data collected in this study will be analyzed using SPSS 26 statistical software. The five subscales and total score of the Wechsler assessment will be analyzed separately. Since multiple comparisons will be made, a multiple comparisons issue may arise. To address this, the Bonferroni correction will be applied, setting the significance level to 0.0167. For other variables, the significance level will be set to 0.05 for analysis.

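### The Bonferroni level of 0.0167 given for the six separately analysed Wechsler scores is 0.05/3; six tests need 0.05/6 = 0.0083

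*Protocol article*

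**What the plan says.** The Statistical analysis section of the protocol article first gives a general rule: "To adjust for multiple comparisons, Bonferroni correction will be applied as needed to control for Type I error". Its last paragraph then turns to the Wechsler test: "The five subscales and total score of the Wechsler assessment will be analyzed separately". It acknowledges that this may raise a multiple-comparisons problem and gives the remedy: "To address this, the Bonferroni correction will be applied, setting the significance level to 0.0167". The next sentence confines that level to the Wechsler: "For other variables, the significance level will be set to 0.05 for analysis".

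The same figure appears in the Sample size section. There the starting point is an alpha of 0.05 ("Initially, the significance level (α) was set at 0.05 for the sample size calculation"), followed by: "However, to account for multiple comparisons, the Bonferroni correction was applied, adjusting the per-comparison significance level to α = 0.0167". The calculation uses three groups and three repeated measurements. Neither section states the number by which 0.05 was divided. The Outcome measures section has the Wechsler given on two occasions and every other measure on three.

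**The concern.** The remedy does not match the problem it is given for. The text names six analyses and offers a threshold that is Bonferroni for three. Bonferroni guarantees the overall error rate only if the divisor is at least the number of tests in the family. With a divisor of three and a family of six, the guarantee is 10%, not 5%.

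What is at stake is the interpretation of individual Wechsler scores. The Discussion presents the quantitative assessment of cognitive change by the Wechsler test as a reason why the study matters. A subscale with p = 0.012, say, would be reported as significant after Bonferroni correction although it fails the correct Bonferroni threshold.

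**Working it through.** **Inputs from the protocol article.** Overall alpha 0.05 (Sample size). Wechsler level 0.0167 (Statistical analysis). Wechsler tests: 5 subscales + 1 total = 6 (Statistical analysis). Effect size f = 0.25, power 0.80, three groups, three measurements, N = 45 before dropout (Sample size). Wechsler measured twice (Outcome measures).

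**Assumptions, because the article gives no values.** Correlation between the six test statistics: 0 to 0.9. Correlation between repeated measurements: 0.5, with 0.3 and 0.7 as a range. Sphericity holds.

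**1. Where 0.0167 comes from.**
- 0.05/3 = 0.0167, which matches the stated figure.
- 0.05/6 = 0.0083, which does not.

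**2. Family-wise error for six tests.**
- Bonferroni bound at 0.0167: 6 × 0.0167 = 0.100.
- Independent tests at 0.0167: 1 − (1 − 0.0167)^6 = 0.096.
- Independent tests at 0.05/6: 1 − (1 − 0.05/6)^6 = 0.049.
- Correlated tests, by simulation of six equicorrelated two-sided z-tests (400,000 draws):

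| Assumed correlation | Error at 0.0167 | Error at 0.0083 |
|---|---|---|
| 0.3 | 8.9% | 4.7% |
| 0.5 | 7.8% | 4.1% |
| 0.7 | 6.2% | 3.3% |
| 0.9 | 4.0% | 2.1% |

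**3. The alternative reading, three pairwise group comparisons.** Three groups give three pairs, and 0.05/3 = 0.0167 is right for the pairs within one score. Six scores × 3 pairs = 18 comparisons. If all 18 were tested at 0.0167 and were independent, the error would be 1 − (1 − 0.0167)^18 = 0.26. A single Bonferroni step over all 18 would need 0.05/18 = 0.0028. On this reading nothing corrects for the six scores.

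**4. The Sample size figure.** For the within-between interaction, λ = f²·N·m/(1 − ρ), df1 = (k − 1)(m − 1) and df2 = (N − k)(m − 1). With k = 3, m = 3, ρ = 0.5 and N = 45, λ = 0.0625 × 45 × 3/0.5 = 16.875 on 4 and 84 df. At alpha 0.0167 the power is 0.815. The smallest N for 80% is 44, or 45 in equal groups, so the plan's 45 reproduces. The 0.0167 was therefore used as the alpha of one interaction F-test with three measurements. Under the Statistical analysis section, the only outcome tested at 0.0167 is the Wechsler, which has two.

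**5. Cost of the correct level for the Wechsler.** With m = 2, N = 45 and ρ = 0.5, λ = 0.0625 × 45 × 2/0.5 = 11.25 on 2 and 42 df.

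| Assumed ρ | Power at 0.0167 | Power at 0.0083 |
|---|---|---|
| 0.3 | 51% | 41% |
| 0.5 | 69% | 59% |
| 0.7 | 92% | 87% |

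**The case against.** The strongest defence is that the divisor is never stated, and that the Sample size section speaks of a per-comparison level in a three-group design. On that reading 0.0167 is the correct level for three pairwise group comparisons, and 0.0083 answers a different question. It stands to this extent: the family is undefined, and 0.0083 alone would not also cover pairwise post-hoc tests. But it does not rescue the text. The Statistical analysis section gives 0.0167 as the answer to analysing six scores separately. It also restricts that level to the Wechsler, although pairwise group comparisons arise for every outcome. If the level was meant for pairs, the six scores have no correction at all.

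A second defence is that the inflation is modest. This is fair as to size. A total score analysed beside its own subscales makes independence implausible, so 9.6% is near the upper end. But Bonferroni is meant to hold whatever the correlation, and the error falls below 5% only when correlation is very high.

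A reader might go further and infer that Type I error is uncontrolled across the trial, because the 12 other instruments are each tested at 0.05 and no primary outcome is identified. The document does not support this as an error. It openly sets 0.05 for those outcomes, says Bonferroni will be used as needed, and claims no trial-wide control. The section mentions primary variables, and their designation may stand in the full protocol or analysis plan, which are not shown.

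A reader might also infer that sizing at 0.0167 while testing other outcomes at 0.05 inflates error. It does not: for those outcomes the sample size is conservative.

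**Conclusion.** The stated Wechsler threshold is wrong for the six tests it is meant to correct. It equals 0.05/3, where 0.05/6 = 0.0083 is needed. The resulting family-wise error is at most 10%, and between 6.2% and 9.6% for assumed inter-test correlations from 0.7 down to 0. The practical consequence is confined to Wechsler scores with p between 0.0083 and 0.0167.

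The threshold and the 10% bound follow from the document's own numbers. The other error rates rest on assumed correlations. The finding does not extend to the other outcomes or to the choice of a primary. The use of 0.0167 in the Sample size section is a matter of clarity about which test is meant, not a further source of error.

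**What to change.** 1. In the Statistical analysis section, test the group-by-time interaction of each of the six Wechsler scores at 0.05/6 = 0.0083, or use Holm over the six p-values. Holm compares the smallest p-value with 0.05/6, the next with 0.05/5, and so on, stopping at the first failure. It controls the same 5% error and loses less power.
2. If 0.0167 was intended for the three pairwise group comparisons, say so, and apply it to the post-hoc tests within each score, in addition to the correction across the six scores.
3. In the Sample size section, state which test the alpha of 0.0167 refers to, since the Statistical analysis section uses that level for the Wechsler only.

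The change is a few sentences and needs no new data. Its cost is power per Wechsler score: about 59% at 0.0083 against 69% at 0.0167, at N = 45, f = 0.25, two time points and an assumed correlation of 0.5 between them. With all 54 children retained, the figures are about 71% against 80%. As recruitment began in May 2024, the change should be made and dated before the Wechsler data are analysed, and the lower power reported rather than recovered by keeping the looser threshold.

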## Discussion

This study will explore the effects of PA and PST on children with ADHD and their primary caregivers. We will focus on understanding how these factors influence the cognitive, emotional, and behavioral functions of the children, along with the emotional and behavioral well-being of their parents.

Numerous intervention studies have shown that children and adolescents with ADHD experience significant improvements in the core symptoms of ADHD through engaging in moderate to vigorous PA and behavioral interventions [12], which generally include aerobic and manipulative activities [6,7,34]. The World Health Organization, the Centers for Disease Control and Prevention (CDC), and the American Academy of Pediatrics recommend behavior therapy for children with ADHD, which includes parent training. This training focuses on creating routines, organizing tasks, managing distractions, and setting goals to improve the child’s functioning. Additionally, a combined approach involving both behavioral therapy and medication has been shown to lead to better outcomes in academic performance, parent-child relationships, and social skills compared to using medication alone [35].

The intervention program’s PA component was explicitly developed to incorporate moderate to high-intensity PA. The PST includes routines, goal setting, positive self-talk, anxiety management, maintaining attentional focus, understanding ADHD, and recognizing the significance of PA. However, children with ADHD may struggle with completing tasks and sustaining attention, which highlights the need for additional support, such as involving parents, to help address these difficulties. Interestingly, a previous study that categorized PA interventions into parent and peer participation groups found that the parent involvement group demonstrated more significant improvements in cognitive, emotional, and behavioral outcomes [33]. This finding highlights the importance of parental involvement in interventions aimed at improving the functioning of children with ADHD, along with the significance of parent training [33,36–40].

Raising a child with ADHD imposes significant stress on parents [41]. This stress can become chronic and long-lasting, significantly negatively affecting the parent-child relationship and emotional well-being [37]. Although parents need psychological or physical interventions to cope with their stress, anxiety, and depression, most interventions are conducted separately for parents and children [21]. Joint participation in PA may encourage ongoing involvement in interventions and improve their overall effectiveness. Studies that compare groups who engage in PA together with those who do not have shown statistically significant improvements in functioning. This suggests that participating together could be a more effective intervention method for parents and children. It allows parents to support their children’s needs without having to dedicate additional time. While improving children’s symptoms is crucial, it’s also important to address maternal symptoms simultaneously. This highlights the importance and rationale for conducting this study.

This study has several potential limitations. First, participant recruitment is restricted to a single region within the metropolitan area, which may limit the generalizability of the findings. Second, the sample size for each group is relatively small, potentially reducing the clinical applicability of the results.

Despite these limitations, this study is significant as it examines the emotional and psychological aspects of both children and parents while quantitatively assessing changes in children’s cognitive performance using the Wechsler test.
